# **I. Post-traumatic stress disorder (optional)** **[POSTTRAUMATIC STRESS DISORDER (optional)]**

(→refers to: go to the diagnosis box, circle "No" on the top of the corresponding diagnosis, and then go to the next question group.)

|    |                                                                                                                                                                                                                                                                                                                                                                                                                 |         |     |
|----|-----------------------------------------------------------------------------------------------------------------------------------------------------------------------------------------------------------------------------------------------------------------------------------------------------------------------------------------------------------------------------------------------------------------|---------|-----|
| I1 | Have you ever experienced, witnessed, or had to deal with an extremely serious traumatic event, such as a real death, or a threat of death or a serious injury to yourself or others?

(Examples of traumatic events: serious accidents, sexual or physical attacks, terrorist attacks, being taken hostage, kidnapping, robbery, fire, discovery of bodies, accidental death, war, natural disasters...) | →
No | Yes |
| I2 | In the past month, have you seen this incident painfully (such as nightmares, deep memories, flashbacks, or physiological reactions)?                                                                                                                                                                                                                                                                           | →
No | Yes |
| I3 | In the past month:                                                                                                                                                                                                                                                                                                                                                                                       |         |     |
|    | a. Have you ever avoided thinking about it or avoiding items that remind you of the incident?                                                                                                                                                                                                                                                                                                                   | No      | Yes |
|    | b. Have you ever had a hard time remembering the important part of what happened?                                                                                                                                                                                                                                                                                                                               | No      | Yes |
|    | c. Are you less interested in your original preferences or social activities than before?                                                                                                                                                                                                                                                                                                                       | No      | Yes |
|    | d. Do you feel that you are alienated or unfamiliar with others?                                                                                                                                                                                                                                                                                                                                                | No      | Yes |
|    | e. Do you notice that your feelings are numb?                                                                                                                                                                                                                                                                                                                                                                   | No      | Yes |
|    | f. Do you feel that your life will be shortened because of this trauma?                                                                                                                                                                                                                                                                                                                                         | No      | Yes |
|    |                                                                                                                                                                                                                                                                                                                                                                                                                 | →       |     |
|    | Is the I3 three or more answer code "Yes"?                                                                                                                                                                                                                                                                                                                                                                      | No      | Yes |
| I4 | In the past month:                                                                                                                                                                                                                                                                                                                                                                                       |         |     |
|    | a. Do you have difficulty sleeping?                                                                                                                                                                                                                                                                                                                                                                             | No      | Yes |
|    | b. Are you particularly prone to anger or temper?                                                                                                                                                                                                                                                                                                                                                               | No      | Yes |
|    | c. Do you have difficulty focusing?                                                                                                                                                                                                                                                                                                                                                                             | No      | Yes |
|    | d. Do you feel nervous or often on alert?                                                                                                                                                                                                                                                                                                                                                                       | No      | Yes |
|    | e. Are you vulnerable to fright?                                                                                                                                                                                                                                                                                                                                                                                | No      | Yes |
|    |                                                                                                                                                                                                                                                                                                                                                                                                                 | →       |     |
|    | Is there 2 or more answers in the I4 code "Yes"?                                                                                                                                                                                                                                                                                                                                                                | No      | Yes |
| I5 | In the past month, have these problems significantly interfered with your work or social activities, or caused obvious pain?                                                                                                                                                                                                                                                                                    | No      | Yes |
|    | Is the I5 code "yes"?                                                                                                                                                                                                                                                                                                                                                                                           |         |     |

|                |     |
|----------------|-----|
| No             | Yes |
| Post-traumatic |     |

|                                                |
|------------------------------------------------|
| Stress disorder
Now suffering |
|------------------------------------------------|

## J. Alcohol abuse or alcohol dependence (ALCOHOL ABUSE AND DEPENDENCE)

*(➔refers to: go to the diagnosis box, circle "No" on the top of the corresponding diagnosis, and then go to the next question group.)*

- |      |                                                                                                                                                                                                                                                                                              |   |    |     |
|------|----------------------------------------------------------------------------------------------------------------------------------------------------------------------------------------------------------------------------------------------------------------------------------------------|---|----|-----|
| J1   | In the past 12 months, have you ever had more than 3 drinkings, and each time you drink more than 30ml of pure alcohol in 3 hours? For example, 56° white wine is more than two, 32° red wine is about 2 two, 20° wine is 3 or so. It can be combined with local drinking habits or customs. | ➔ | No | Yes |
| 
 |                                                                                                                                                                                                                                                                                              |   |    |     |
| J2   | In the past 12 months                                                                                                                                                                                                                                                                 |   |    |     |
|      | a. Do you need to drink more wine to get the feeling of your initial drink?                                                                                                                                                                                                                  |   | No | Yes |
|      | b. Have you ever had hand shaking, sweating or feeling uneasy when you are reducing your alcohol consumption? Or, do you drink to avoid these symptoms or avoid headaches after drinking, such as "hand shake", sweating or restlessness? If one answer is "yes", the code is "yes".         |   | No | Yes |
|      | c. When you drink, do you actually drink more than originally expected?                                                                                                                                                                                                                      |   | No | Yes |
|      | d. Have you ever tried to reduce alcohol consumption or stop drinking but did not succeed?                                                                                                                                                                                                   |   | No | Yes |
|      | e. Do you spend a lot of time looking for wine, drinking or sobering during the day of drinking?                                                                                                                                                                                             |   | No | Yes |
|      | f. Have you reduced your work, your preferences, or the time you spend with others because you drink?                                                                                                                                                                                        |   | No | Yes |
|      | g. Even if you know that drinking has caused you health or mental problems, continue to drink?                                                                                                                                                                                               |   | No | Yes |

*J2 three or more answers code "yes"?*

*Is the patient's alcohol dependence code "yes"?*

|                                                   |     |
|---------------------------------------------------|-----|
| No                                                | Yes |
| Alcohol dependence
Now suffering |     |

➔

No      Yes

**J3 In the past 12 months**

a. Have you ever been drunk, excited after drinking, or in the aftereffects of alcohol when you study at school, work at work, or do housework at home? What caused this problem?

*Only "Yes" is encoded when the problem is caused.*

b. Have you ever been involved in life-threatening activities such as driving a car, riding a motorcycle, operating a machine, rowing, etc. after being drunk?

c. Have you ever had an illegal problem with drinking, such as being arrested or harassing law and order?

d. Even though drinking has already caused problems with your family or other people, do you still drink alcohol?

*J3 has 1 or more than answered "yes"?*

|               |     |
|---------------|-----|
| No            | Yes |
| Alcohol abuse |     |
| Now suffering |     |

## **K. Non-alcoholic psychoactive substance use disorder (NON-ALCOHOL PSYCHOACTIVE SUBSTANCE USE DISORDERS)**

*(This question group is mainly for the study of the use of related substances or for the use of high-risk groups. Only the generic name is translated and listed in the original "common name (trade name)". It is recommended that the researcher should address the local situation when needed. Ask the interviewee with the generic name/common name/commodity name.)*

**(→refers to: go to the diagnosis box, circle "No" on the top of the corresponding diagnosis, and then go to the next question group.)**

|    |                                                                                                                                                                                                                                                                                            |   |    |     |
|----|--------------------------------------------------------------------------------------------------------------------------------------------------------------------------------------------------------------------------------------------------------------------------------------------|---|----|-----|
| K1 | Now I want to show you (showing a card for psychoactive substances) or give you a list of drugs or drugs (read the list below). In the past 12 months, have you used more than one of these drugs to achieve the feeling of "floating", making yourself feel better or changing your mood? | → | No | Yes |
|----|--------------------------------------------------------------------------------------------------------------------------------------------------------------------------------------------------------------------------------------------------------------------------------------------|---|----|-----|

*Circle each drug you have taken:*

Stimulants: amphetamines, such as ice, dextroamphetamine, methylphenidate (Ritalin), diet pills.

Cocaine: snorting, IV, freebase, crack, "speedball".

Anesthetics: heroin, morphine, hydromorphone hydrochloride, opium, methadone, codeine, compound oxycodone, propoxyphene hydrochloride

Hallucinogen: LSD (acid), mescaline, penicillin, benzocyclidine (PCP) ("Angel Dust", "peace pill", psilocybin, STP, "mushrooms", ecstasy, MDA, or MDMA, Ktamine("special K")

Inhalants: "glue", ethyl chloride, "rush", nitrous oxide ("laughing gas"), amyl or butyl nitrate ("poppers").

Cannabis: hashish ("hash"), THC, "pot", "grass", "weed", "reefer".

Sedatives: quaalude, Seconal ("reds"), Valium, Xanax, Librium, Ativan, Dalmane, Halcion, Barbiturate, Miltown, GHB, Roofinol, "roofies".

Other: steroids, over-the-counter hypnosis, diet pills or cold medicines, etc., any other medicine

*Indicate the most used drugs:*

- *If multiple substances are used simultaneously or sequentially:*

*Each used drug (or a class of drugs)*

€

*Only investigate the most commonly used drugs (or a class of drugs)*

€

- *If only one drug (or one class of drugs) is used:*

*Only investigate one drug (or one class of drugs) that has been used*

€

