### 5.2 Exclusion criteria

- (1) Allergic or known to be allergic to venlafaxine and desvenlafaxine;
- (2) Subjects with MDD who were not responsive to the previous venlafaxine treatment with sufficient amount and duration and to at least two different mechanisms of action antidepressants with adequate amount and duration in the past;
- (3) There is a clear suicide attempt or behavior and score of the 10th item (suicidal ideation) in MADRS scale is 4 points or greater;
- (4) Pregnant or lactating women, women who have a planned pregnancy in the near future;
- (5) Subjects meet the diagnostic criteria for other psychotic disorders(except for MDD) in DSM-5, such as Schizophrenia Spectrum and Other Psychotic Disorders, Bipolar and Related Disorders, Obsessive-Compulsive and related Disorders, post-traumatic stress disorder, separation disorders, anorexia nervosa or bulimia and personality disorder;
- (6) Subjects who meet the diagnostic criteria for substance or alcohol abuse (excluding nicotine or caffeine) 6 months prior to the screening;
- (7) MDD secondary to other mental illnesses or physical illnesses;
- (8) Those with a history of seizures (except for convulsions caused by febrile seizures in

children);

(9) Receiving electroconvulsive therapy (ECT) within 3 months prior to screening or according to the investigator's judgment that ECT is currently required;

(10) Those who have received systematic psychotherapy (interpersonal relationship therapy, dynamic therapy, cognitive behavioral therapy) within 3 months of screening;

(11) Those who have received transcranial magnetic stimulation (TMS) 3 months prior to screening;

(12) Those who have received light therapy 2 weeks prior to screening;

(13) Those who have stopped psychotropic drugs for less than 7 half-lives prior to study randomization (monoamine oxidase inhibitor for at least 2 weeks, fluoxetine for at least 1 month);

(14) Those with seriously unstable cardiovascular, liver, kidney, blood, endocrine and other physical diseases or a medical history;

(15) Hypertensive patients with poor blood pressure control ( $SBP \geq 140$  mmHg or  $DBP \geq 90$  mmHg at screening);

(16) There is a history of gastrointestinal disease known to interfere with drug absorption or excretion or a history of surgery known to interfere with drug absorption or excretion;

(17) A history of increased intraocular pressure or narrow-angle glaucoma;

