## ● Provisions:

Sentences written in ordinary Song dynasty should be accurately read to the patient to standardize the diagnostic evaluation process.

Sentences written in *italics* do not need to be read to the patient. This is a guide to the examiner to help the examiner score during the diagnosis.

Sentences written in **bold** indicate the time frame of the survey, and the examiner should read as many times as possible. Only symptoms that occur within the time frame of the survey should be considered in scoring.

The sentence (underlined in brackets) is a clinical example of the symptom that helps to further explain the problem and can be read to the patient.

The answer with an arrow (➔) above indicates that the criteria necessary for a diagnosis are not

met. In this case, the inspector should go back to the end of the question group, circle "No" in all the diagnostic boxes, and then proceed to the next question group. ➔

When a word is separated by a slash "/", the interviewer should read only those symptoms that the patient has (eg, question A3).

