***Does K2 have 3 or more answer codes "Yes"?***

*Indicate the drug used:*

|                        |     |
|------------------------|-----|
| No                     | Yes |
| Drug dependence |     |
| Now suffering   |     |

[figure not shown]

*Is the code for patient drug abuse "yes"?*

No Yes

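### Annex 9, MINI module K: the printed K1 gate turns away users of a single drug, against the module's own single-drug branch and exclusion 6, and the step before K3 names the wrong diagnosis

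*Protocol*

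**What the plan says.** **The gate.** Annex 9, module K, opens with K1. After the interviewee has seen or heard a list of drugs, the interviewer asks about the past 12 months: "have you used more than one of these drugs to achieve the feeling of" floating, or to feel better or change mood. An arrow stands over No.

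**What the arrow does.** The header of module K says that the arrow sends the interviewer to the diagnosis box, to circle No "on the top of the corresponding diagnosis, and then go to the next question group". The general Provisions of Annex 9 say the same for a whole question group: No is circled "in all the diagnostic boxes, and then proceed to the next question group".

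**The branch after the gate.** Below the drug list, the form tells the interviewer which drug to pursue. One branch begins "If only one drug (or one class of drugs) is used" and instructs: "Only investigate one drug (or one class of drugs) that has been used".

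**The step between K2 and K3.** It asks "Is the code for patient drug abuse" yes. The corresponding step in module J, between J2 and J3, asks "Is the patient's alcohol dependence code" yes.

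**The eligibility rule.** Exclusion 6 in section 5.2, repeated in the Summary, reads: "Subjects who meet the diagnostic criteria for substance or alcohol abuse (excluding nicotine or caffeine) 6 months prior to the screening". Section 7.1 lists the MINI among the Visit 1 procedures.

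**The concern.** A gate question decides who is asked anything further. If it counts drugs rather than any use, a patient who misuses one sedative or one opioid can truthfully answer No, and the form then records the absence of both drug dependence and drug abuse without a single criterion having been asked. The form's next page assumes that such patients are still in the module.

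At stake is the reliability of one input to exclusion 6. The MINI is the only structured diagnostic interview listed at Visit 1, and the laboratory tests in section 8.2.4 and in the notes to the visit schedule contain no drug screen that could correct a false negative. The Provisions of Annex 9 also tell interviewers to read the standard questions out exactly, so following the form faithfully reproduces the error. The primary endpoint is a mood scale, and exclusion 6 exists to keep people with substance abuse out of the randomised population.

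**Working it through.** No calculation in the plan bears on this point. The check is a trace of the skip logic, then a comparison with the neighbouring module and with the exclusion criterion.

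**1. K1 as printed.**

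| Listed drugs used in the past 12 months | Literal answer to K1 | K2 and K3 asked? | Dependence and abuse boxes | Single-drug branch reached? |
|---|---|---|---|---|
| None | No | No | Both No, as intended | No |
| Exactly one | No | No | Both No, whatever K2 and K3 would have shown | No |
| Two or more, same class | Yes | Yes | Set by K2 and K3 | Yes, as one class |
| Two or more, different classes | Yes | Yes | Set by K2 and K3 | No |

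The second row is the fault. The branch for a single drug or single class can be reached only by people who used several drugs of one class. Those who used one drug, whom it names first, have already left the module.

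**2. Is the number of drugs a criterion anywhere else?** No. K2 and K3 are put for one selected drug or drug category. Dependence needs three or more positive K2 items, and abuse needs at least one positive K3 item. Neither depends on how many substances were used. Only K1 carries such a condition, and it conflicts with everything behind it in the module.

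**3. The step before K3.** The order printed in module K is K2, the dependence box, the intermediate step, K3, the abuse box. The intermediate step asks whether abuse is coded yes, but at that moment abuse has not been coded. The order in module J is the same (J2, dependence box, intermediate step, J3, abuse box), and there the step asks about dependence, which has just been coded. The module K step therefore cannot be answered as worded. A graphic next to this line is missing from the text at hand, so nothing is claimed about where each answer leads; the point rests on the wording.

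**4. Against exclusion 6.** The criterion speaks of substance or alcohol abuse, excepts nicotine and caffeine, and sets no minimum number of substances. A patient who abuses one listed drug falls under it, yet the printed module records that patient as negative.

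**5. What else at screening bears on exclusion 6.** Visit 1 (section 7.1) separately lists medical history with prior treatment, diagnosis by DSM-5 criteria, review of concomitant medication and confirmation of the eligibility criteria. Visit 2 repeats the eligibility check. Exclusion 6 does not name the MINI as its source. Its window is 6 months, whereas module K looks back 12 months, so the module K box alone could not settle the criterion in any case.

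**The case against.** The strongest reply is that this is a translation fault and not a feature of the trial. Annex 9 calls itself the Chinese edition, and its Translator's note describes a translation from English into Chinese, evaluated for reliability and validity, with high agreement with SCID-P on several diagnoses including substance dependence. The English text is visibly corrupt elsewhere: penicillin is listed among the hallucinogens, for example. K1 may have turned a count of occasions into a count of drugs; the alcohol gate J1 counts drinking occasions. If the Chinese form reads correctly, no patient was ever misrouted. This stands, and it determines the order of the remedy. It does not remove the contradiction in the document as issued.

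A second reply is that trained raters would notice. Section 12 requires training in the psychiatric interview, the form tells the rater to circle each drug taken, and the single-drug branch is directly in view. This lowers the risk, but it relies on raters departing from a question they are told to read exactly.

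A third is that the header of module K describes it as mainly for substance studies or high-risk groups. That is so, but the protocol schedules the MINI without exempting module K, and the diagnostic record table marks other modules as optional and not this one.

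On the step before K3, it can be said that the dependence box just above makes the meaning plain. The intention is indeed recoverable; the wording is still wrong.

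**Conclusion.** The printed module K contradicts itself and does not match exclusion 6. Applied literally, K1 codes every user of exactly one listed drug negative for dependence and abuse without asking K2 or K3, and the step before K3 refers to a diagnosis that has not yet been made. Both statements follow from the protocol alone and need no outside version of the instrument.

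Three stronger readings are tempting and are not supported:

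- *Exclusion 6 rests on this module, so single-drug misusers were enrolled.* The criterion does not name the MINI and uses a different time window, and history, DSM-5 diagnosis and two checks of eligibility apply as well. This is a risk of missed exclusions, not a certainty.
- *A number of the 558 planned patients can be put on it.* That would need the prevalence of drug misuse among candidates, the share who use one drug only, and the share whom the other screening steps miss. The documents give none of these, so no count is offered.
- *The Chinese form used at sites has the same fault.* That form is not in the protocol. The agreement reported in the Translator's note gives some reason to think it may not.

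Sample size, power, alpha and the analysis are unaffected. This is a wording error in a screening instrument, worth correcting because it bears on eligibility and costs almost nothing to put right.

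**What to change.** 1. First compare the printed Annex 9 with the Chinese MINI form used at sites, at K1 and at the step between K2 and K3.
2. In every version that carries the error, reword K1 so that use of any one listed drug passes the gate. It then agrees with the single-drug branch and with exclusion 6.
3. In the same versions, change the step before K3 to ask whether drug dependence is coded yes, as module J does for alcohol.
4. If the site form is correct, an erratum to the English annex is enough. If it shares the K1 wording, notify sites and re-ask K1, with K2 and K3 where it is then positive, but only of subjects screened on that form.

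The cost is one document comparison, two wording corrections and, if needed, a site notice. No visit, procedure or analysis is added; where K1 was faulty, a few more candidates would go on to K2 and K3.
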